## Results

In December 2021, the clinical trial registration was approved. Recruitment and data collection for the trial is ongoing, and the results of this study are likely to be published in late 2024.

## Discussion

### Potential Impact and Significance of the Study

The role of exercise training in individuals with moderate to severe asthma has been widely studied in recent years [47,48]. Aerobic exercise training improves physical fitness, health-related quality of life, asthma control, and lung function in this population [46,49]. However, despite the beneficial effects of exercise training, little is known about the behavioral modifications needed to achieve a more active lifestyle [4], and studies have been conducted to address behavioral interventions. Very recently, it was demonstrated that a behavioral intervention aimed at increasing PADL modified the behavior of patients with asthma, resulting in an increase in PADL and improvement in symptoms of the disease [5]. This protocol was developed to identify the characteristics of individuals who respond and do not respond to this type of intervention, which may help guide clinical practice.

### Strengths and Limitations of the Study

In addition to the potential to identify the characteristics of responders and nonresponders, this study will also follow up 4 months after training, considered the medium term. These results will allow us to determine if behavioral changes are maintained in the responders over time. The assessment of PADL using accelerometers as a primary outcome is a study strength because it is an objective outcome measure, thus decreasing the risk of bias. The fact that the study will be performed in only 1 hospital center can be considered a limitation.

### Contribution and Clinical Applicability

To our knowledge, this will be the first study to assess the characteristics of responders and nonresponders to a behavioral intervention aimed at increasing PADL in adults with asthma. Therefore, the results obtained in the proposed protocol may provide vital information for health care professionals to refer patients with asthma to more specific intervention approaches (behavioral or otherwise) based on their profile as potential responders or nonresponders. Furthermore, this study may clarify whether the potential gains obtained in the short term after the intervention are maintained in the medium term in individuals with moderate to severe asthma.

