**Objective:**

This study aims to (1) identify the characteristics of adult responders and nonresponders with asthma to a behavioral intervention to increase physical activity and (2) evaluate the functional and clinical benefits in the medium term.

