**Methods:**

This prospective pragmatic study will include adults with moderate to severe asthma who enroll in a behavioral intervention. All individuals will receive an educational program and an 8-week intervention to increase PADL (1 time/wk; up to 90 min/session). The educational program will be conducted in a class setting through group discussions and video presentations. Behavioral interventions will be based on the transtheoretical model using counseling, incentives, and individual feedback aiming to increase participation in physical activity. Motivational interviewing and guidelines for overcoming barriers will be used to stimulate individuals to reach their goals. Pre- and postintervention assessments will include the following: PADL (triaxial accelerometry), body composition (octopolar bioimpedance), barriers to PADL (questionnaire), clinical asthma control (Asthma Control Questionnaire), quality of life (Asthma Quality of Life Questionnaire), anxiety and depression levels (Hospital Anxiety and Depression Scale), and exacerbations. “Responders” to the intervention will be defined as those who demonstrate an increase in the number of daily steps (≥2500).

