**Conclusions:**

The intervention will likely promote different effects according to the clinical characteristics of the individuals, including asthma control, age, anxiety and depression levels, obesity, and several comorbidities. Identifying individuals who respond or do not respond to behavioral interventions to increase PADL will help clinicians prescribe specific interventions to adults with asthma.

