## Methods

### Study Design

This prospective cohort study will be conducted at a university hospital that provides specialized asthma treatment. The study protocol was developed following the SPIRIT (Standard Protocol Items: Recommendations for Interventional Trials) checklist guidelines [14], and the trial was registered at ClinicalTrials.gov (NCT05159076). The study design is illustrated in Figure 1. Individuals with asthma will be enrolled in the trial after a routine medical consultation. Baseline lung function will be checked from the medical records. Eligible participants will undergo an 8-week behavioral intervention protocol to increase PADL and reduce sedentary behavior. First, all included individuals will receive an educational program, followed by an intervention aimed at increasing physical activity. All individuals will be assessed before and after the 8-week intervention and then 16 weeks later. The outcomes assessed will include anthropometric variables, clinical asthma control, health-related quality of life, physical activity levels, anxiety and depression symptoms, exacerbations, body composition, barriers to performing PADL, and physical activity behavioral stages (Figure 1).

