### Statistical Analysis Planning

Individuals will be stratified as “responders” and “nonresponders” based on an increase of ≥2500 steps [45]. The Kolmogorov-Smirnov test will be used to assess data normality. Cluster analysis will be used to characterize the groups according to individual characteristics. Cluster analysis will be carried out in 2 stages: hierarchical analysis using the Ward method to determine the number of clusters and k-means analysis to group the clusters [46]. Comparisons of clinical, anthropometric, and psychosocial data obtained in the responder and nonresponder groups will be conducted using the 2-tailed *t* test or Mann-Whitney *U* test for continuous variables and the chi-square test for categorical variables. To determine the independent factors associated with the level of PADL (dependent variable, considering clinical control, smoking, obesity, anxiety, and depression as independent variables), multiple linear regression analysis (stepwise forward) will be used. The intra- and between-group comparison at baseline, short term, and medium term will be assessed using the 2-way ANOVA with repeated measures test. The significance level will be adjusted to 5% (*P*<.05) for all tests. If necessary, intention-to-treat analysis will be performed, as described earlier. SPSS Statistics (version 22.0; IBM Corp) will be used for statistical analysis. Data integrity will be monitored by regularly scrutinizing data files for omissions and errors. Participants will be given an anonymous study ID to protect confidentiality, and only study investigators will have access to the final trial data set.

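### With one treated group and no comparator, the study can find characteristics that go with a ≥2500-step rise, but not characteristics that modify the programme's effect or support choosing between approaches

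*Protocol article*

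**What the plan says.** The design has a single group. Study Design states "This prospective cohort study will be conducted at a university hospital that provides specialized asthma treatment" and that "all included individuals will receive an educational program, followed by an intervention aimed at increasing physical activity"; the Abstract's Methods say the same ("All individuals will receive an educational program and an 8-week intervention to increase PADL"). No control, waiting-list or alternative-treatment group is described, and the Allocation row of Table 2 carries no tick.

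Statistical Analysis Planning sets the grouping: "Individuals will be stratified as “responders” and “nonresponders” based on an increase of ≥2500 steps". It then plans t, Mann-Whitney or chi-square tests between these two groups, a cluster analysis of individual characteristics, a stepwise linear regression on the level of physical activity, and a two-way repeated-measures ANOVA over the three time points.

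The stated aims and uses are wider:
- The last paragraph of the Introduction hypothesises that the intervention might have different effects depending on patients' clinical characteristics. The Abstract's Conclusions repeat this as likely, and the closing Conclusion as possible.
- The Abstract's Objective is to "evaluate the functional and clinical benefits in the medium term". The Introduction speaks more neutrally of responses.
- The Abstract's Conclusions and the closing Conclusion say that identifying responders and nonresponders "will help clinicians prescribe specific interventions to adults with asthma".
- Contribution and Clinical Applicability says the results may help professionals "refer patients with asthma to more specific intervention approaches (behavioral or otherwise) based on their profile as potential responders or nonresponders".

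Strengths and Limitations of the Study names one limitation: "The fact that the study will be performed in only 1 hospital center can be considered a limitation".

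**The concern.** Saying that an intervention works differently in different kinds of patient is a statement about effect modification. Choosing between this programme and another approach by profile needs more: the effect of one relative to the other must differ by profile. Both need information on what similar patients do without the programme, or with something else. This study collects none.

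A characteristic that only goes with step change in general will look the same as one that alters the effect of the programme. If it is reported under the present wording, it becomes a profile of patients who do or do not respond to the intervention and a basis for prescribing. Patients with a nonresponder profile might gain as much from the programme, relative to other care, as anyone else. The data could not show it either way.

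**Working it through.** **1. The plan's own figures.** Inputs from Sample Size Calculation: difference 2500 steps, SD 2500, α 5%, power 80%, nonresponder share 17%. A two-sided t test at a standardised difference of 2500/2500 = 1 needs 16.7 per group, rounded up to 17. Then 17/0.17 = 100. Both stated figures reproduce. They size a comparison between two subgroups that were both treated, not a difference in treatment effect.

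**2. What the data can identify.** For a patient with trait X, write

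mean change under the programme = mean change under other care + effect of the programme.

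Only the left side is observed. Three hypothetical cases, in steps per day (other care + effect = observed):

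| Case | Trait present | Trait absent |
|---|---|---|
| A: same effect in all | 1500 + 2500 = 4000 | 0 + 2500 = 2500 |
| B: effect larger with the trait | 0 + 4000 = 4000 | 0 + 2500 = 2500 |
| C: effect smaller with the trait | 2500 + 1500 = 4000 | 0 + 2500 = 2500 |

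The observed means are the same in all three. Patients with the trait would more often be called responders in each, yet in C they gain less from the programme. Even the direction of effect modification is not identified.

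**3. Whether a planned analysis gets round this.** The two-group tests compare treated patients with treated patients. The clustering groups treated patients by their characteristics. The regression can contain no treatment term, because treatment does not vary. The between-group factor in the ANOVA is responder status. None supplies the missing term, and no later analysis plan could, because the data will not exist.

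**4. Illustration, continuous trait.** Assumptions: N = 100; SD 2500 taken as the SD of change (the article does not say that it is); the same effect in every patient; change = μ + 2500·(r·X + √(1−r²)·e), with X and e standard normal; two-sided pooled t test of X at 5%; 20,000 simulated studies per setting. μ = 4885 gives an 83/17 split and μ = 2500 a 50/50 split.

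| r with total change | 83/17 split | 50/50 split |
|---|---|---|
| 0 | 5.0% | 5.2% |
| 0.1 | 9.7% | 12.8% |
| 0.2 | 26.8% | 36.0% |
| 0.3 | 52.3% | 68.1% |
| 0.4 | 78.1% | 91.0% |

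A fresh run agreed to within one percentage point.

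**5. Illustration, binary trait.** Trait in 50% of patients, chi-square test, 4000 runs. With an identical effect of 2500 steps in everyone, a trait that shifts step change by 1000, 1500 or 2500 steps whatever the treatment is significant in 37%, 68% and 98% of runs. With zero effect the rates are 27%, 51% and 91%. A trait-by-arm interaction test on 100 patients randomised 1:1 stays between 4.5% and 5.6% in every setting run.

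**6. What a test of effect modification would take.** For scale only, to detect a 2500-step difference in effect (SD 2500, 1:1 randomisation, two-sided 5%, 80% power), with trait prevalence p:

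N = 4·(1.96 + 0.842)²·(1/p + 1/(1−p))·(2500/2500)²

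This gives 126 at p = 0.5, 150 at p = 0.3 and 223 at p = 0.17. With 100 randomised, power would be about 71%, 63% and 47%.

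**The case against.** **The text is hedged.** This is partly right. The referral sentence says may, and so do the hypothesis and the closing Conclusion on differing effects. A reader might infer that the article promises to steer patients between approaches; it does not go that far. But the sentence that the results will help clinicians prescribe is unhedged in both places. The hedges also concern whether effects differ, not whether this design could tell.

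**A prognostic use is legitimate.** This stands. Knowing who is unlikely to reach the step target in this programme is useful, and one treated cohort can inform it. It does not show that another approach would serve those patients better.

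**Average benefit was shown in the earlier study the article cites.** An average benefit does not show that the benefit varies by profile.

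**The simulated rates are largely assumed.** This also stands. They are the power of the planned test under chosen correlations with total change. If the SD of background change were half the total SD (also an assumption), a correlation of 0.3 with background change becomes 0.15 with observed change, and the rate at 83/17 falls from 52% to 17%. Entry criteria of low activity, 30 days of clinical stability and maintained pharmacotherapy may limit background change, and the article gives no figure for it. The argument in step 2 uses none of these numbers.

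**The design is openly a single-group cohort.** True, and that is no fault in itself. The fault lies in the claims attached to it.

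**Conclusion.** The concern holds for what the study may conclude. Within one treated cohort, the planned analyses can identify baseline characteristics associated with a rise of at least 2500 steps during the programme. They cannot identify modifiers of its effect, nor support a choice between this programme and another. The statements on differing effects, prescribing and referral go beyond the design. This rests only on the absence of a comparator, which the article makes plain.

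The size of the problem in practice is unknown. The rates of 27%, 52% and 78% illustrate how readily a purely prognostic trait could be flagged; they depend on assumed correlations and on treating SD 2500 as an SD of change.

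Three stronger readings are tempting and not supported. The documents do not say that the programme would be withheld from patients with a nonresponder profile. They do not show that a merely prognostic trait exists, so it cannot be said that one will be reported. And the missing comparator does not invalidate the study for its descriptive aim.

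**What to change.** 1. Restate the first objective, and the hypothesis in the Introduction, as identifying baseline characteristics associated with a rise of at least 2500 steps during the programme.
2. In the Abstract's Objective, replace benefits with the neutral term the Introduction already uses, or with before-after change.
3. In the Abstract's Conclusions, in Contribution and Clinical Applicability and in the closing Conclusion, state that the profiles are prognostic and hypothesis-generating until tested as a profile-by-treatment interaction in a controlled study.
4. In Strengths and Limitations of the Study, name the missing comparator. Doing only this would leave the claims as they are, so it does not replace items 1 to 3.

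The cost is wording and a more modest claim. Recruitment, assessments and planned analyses are unchanged.

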### Conclusion

The behavioral intervention to increase PADL may promote different effects according to the clinical characteristics of the individuals, including asthma control, age, anxiety and depression levels, obesity, and several comorbidities. Furthermore, identifying individuals who respond or do not respond to behavioral interventions to increase PADL will help clinicians prescribe specific interventions to adults with asthma.

## Abbreviations

ACQ: Asthma Control Questionnaire
AQLQ: Asthma Quality of Life Questionnaire
GINA: Global Initiative for Asthma
HADS: Hospital Anxiety and Depression Scale
PADL: physical activity in daily life
SPIRIT: Standard Protocol Items: Recommendations for Interventional Trials
WHO: World Health Organization
